## Abstract

**Background:**

Diabetic foot ulcers (DFUs) present a formidable challenge to both patients and health care systems. DFUs significantly reduce the quality of life for patients, prolong hospital stays, and are the cause of approximately 70,000 lower limb amputations across the globe annually. Prevention of DFUs primarily involves the optimization of blood sugar levels and the effective management of complications, particularly peripheral neuropathy. Golden Rice has been proven to lower blood sugar levels due to its beta-carotene content, and Piper crocatum (*P. crocatum*) has been found to be effective in reducing the risk factors of DFUs through biomolecular regulation because of its polyphenol content.

**Objective:**

The principal objective of this study is to identify the efficacy of *P. crocatum*–enriched cookies, with Golden Rice as their primary ingredient, in preventing DFUs. The evaluation will center on their impact on the expression of matrix metalloproteinase-9 (MMP-9), a pivotal factor in the development of DFUs.

**Methods:**

This study is an experimental clinical research that follows the randomized controlled trial method and uses a single-blind design. The participants in the study are outpatients from primary health centers in Makassar, Indonesia, who have been diagnosed with diabetes mellitus. The sample for the study will be randomly selected and subsequently categorized into 2 groups: the intervention group and the control group. The intervention group consumes *P. crocatum*–enriched Golden Rice cookies, while the control group receives cookies without these additives. The participants from both groups will consume their respective cookies (packaged identically) twice a day for 14 days. The cookies will be prepared according to a modified recipe with an emphasis on low glucose content, resulting in 51 calories per cookie, comprising 1% carbohydrates, 6% fat, 4% cholesterol, and 4% fiber, excluding gluten, sugar, and salt. They will be baked at 158°C for 20 minutes. The process involves the addition of 20% Golden Rice and 10% *P. crocatum* ethanol extract, both prepared via maceration with 96% ethanol. The dependent variable in this study is the expression of gelatinases matrix metalloproteinase, to be assessed at 2 distinct time points—preintervention (pretest) and postintervention (posttest)—with the evaluation conducted through the western blotting method.

**Results:**

The recruitment and testing phase started in January 2024. The study is scheduled to be completed by the end of March 2024. Data analysis will commence in April 2024, and the publication of the results is anticipated in the same year (2024). The study will report on the changes in primary data, encompassing gelatinases matrix metalloproteinase, as well as secondary data, including the ankle-brachial index, neuropathy score, and random blood glucose level.

**Conclusions:**

The findings of this trial are expected to significantly impact the selection of strategies by health care practitioners to enhance diabetes self-management, particularly in the domain of therapeutic snacking, for patients diagnosed with diabetes mellitus.

**Trial Registration:**

Thai Clinical Trials Registry TCTR20230502001; https://www.thaiclinicaltrials.org/show/TCTR20230502001

**International Registered Report Identifier (IRRID):**

PRR1-10.2196/49940

## Introduction

Diabetic foot ulcer (DFU) is a major problem in patients with diabetes, affecting 15% of the diabetic population. DFUs significantly reduce the quality of life for patients, prolong hospital stays, and are the cause of approximately 70,000 lower limb amputations across the globe each year [1]. Diabetic foot disease is among the top 10 medical conditions in terms of burden, and it is estimated that up to 34% of individuals with diabetes will experience DFU at some point in their lives [2]. Preventing DFUs and amputations is of utmost importance to alleviate this significant burden on patients, health care systems, and society as a whole [3].

Peripheral neuropathy, the most prevalent type of diabetic neuropathy, primarily affects the nerves in the extremities, especially the feet. It accounts for 6.4% of all complications related to diabetes [4]. This condition predominantly disrupts sensory function, leading to gradual numbness, which increases the susceptibility to developing ulcers due to external injuries. It is crucial to identify these risk factors to enhance the effectiveness of preventive measures for DFUs [5]. Treating diabetic neuropathy presents a significant clinical hurdle. According to some studies, the gelatinase matrix metalloproteinase 9 (MMP-9) has been found to play a vital role in the demyelination of axons and the development of diabetic neuropathy in rodents [6,7]. As gelatinase MMP-9 plays a pivotal role in the initial onset of neuropathy, it is considered crucial in the progression of diabetic neuropathy and could potentially be targeted for treatment purposes [6,7].

Elevated levels of blood sugar and insulin resistance in patients with type 2 diabetes further contribute to the generation of reactive oxygen species (ROS), which intensifies the complications associated with this disease [8]. The activity of vascular MMP-9 is heightened in individuals with diabetes mellitus, partly due to increased production by vascular endothelial cells. Additionally, the activity of ROS plays a significant role in this process [9]. The high levels of ROS and MMP-9 have been found to be associated with glycemic index and diabetes complications [10].

Different types of diabetic-friendly cookies and breads are already in circulation, such as cassava bread, flax meal powder, and grape seed oil bread. However, their purpose is solely to limit glucose intake rather than directly affecting insulin levels. In contrast, noncookie products made with Golden Rice as the main ingredient contain beta-carotene, which can stimulate insulin production in the body by boosting the beta pancreas and decreasing the glycemic index [11]. However, the reduction in glycemic index needs to be supported by the biomolecular environment as an effort to prevent DFUs. The suitable herbal ingredient for combination in these cookies is *Piper crocatum (P. crocatum*). The oral consumption of *P. crocatum*, belonging to the Piperaceae family, has been proven safe among the population in Indonesia [12].

The use of *P. crocatum* has been documented to exhibit numerous therapeutic activities, such as anti-inflammatory effects. It has shown to reduce the expression of tumor necrosis factor alpha, nitric oxide, and interleukin-1β in a liver injury model using rats [13]. In addition, *P. crocatum* also exhibits wound healing activities by increasing the expression of superoxide dismutase 1, alpha-smooth muscle actin, and E-cadherin, and reducing p53 in hyperglycemic fibroblasts [14]. It has antibacterial properties when used topically [15]. *P. crocatum* acts as an antioxidant by reducing the expression of ROS and increasing glutathione peroxidase and cytochrome P450 2E1 [16]. It also demonstrates antihyperglycemic effects when administered orally [17].

Based on relevant studies on *P. crocatum* and its various mechanisms, *P. crocatum* can be used as a base ingredient for cookie-based therapies for the prevention of DFU. If the reduction of MMP-9 is recognized as a beneficial therapeutic target for DFU treatment [18], MMP-9 would also be a favorable target for DFU prevention. This is because the activity and expression of vascular MMP-9 in patients with diabetes mellitus are inherently elevated [19]. Furthermore, the gelatinase MMP-9 plays a crucial role in the pathogenesis of diabetic neuropathy through axonal demyelination, which is one of the risk factors for DFU [6]. Therefore, this study aims to identify the effectiveness of *P. crocatum* cookies with Golden Rice as the main ingredient for preventing DFUs through the regulation mechanism of MMP-9.

## Methods

### Study Design

This randomized controlled trial will be conducted at a public health center in Makassar, Indonesia, following a 2-arm, parallel-group, randomized, double-blind, placebo-controlled design. The study protocol was developed in accordance with the SPIRIT (Standard Protocol Items: Recommendations for Interventional Trials) 2013 checklist (Multimedia Appendix 1). Figure 1 shows the flowchart detailing participant enrollment, allocation, intervention, and assessment, and Table 1 presents the participant timeline.

**Figure 1 figure1:**
[figure not shown]
The CONSORT (Consolidated Standards of Reporting Trials) flowchart for participant recruitment and progress through a randomized controlled trial investigating the efficacy of Golden Rice cookies with Piper crocatum (*P. crocatum*) active extract in preventing foot ulcers among patients with diabetes at a public health center in Makassar, Indonesia, from November to December 2023.

**Table 1 table1:** Participant timeline in a randomized controlled trial investigating the efficacy of Golden Rice cookies with Piper crocatum active extract in preventing foot ulcers among patients with diabetes at a public health center in Makassar, Indonesia, from November to December 2023.

Activities		Enrollment	Allocation	Postallocation			Close-out
		Week 1	Week 2	Week 3	Week 4	Week 5	
**Enrollment**							
	Eligibility screening	✓					
	Informed consent	✓					
	Randomization		✓				
	Allocation		✓				
	Patients training		✓				
**Intervention**							
	Supplementation			✓	✓		
	Compliance			✓	✓		
	Adverse events			✓	✓		
**Assessment**							
	Demographics		✓			✓	
	Clinical information		✓			✓	
	Neuropathy score		✓			✓	
	Ankle-brachial index		✓			✓	
	Random blood glucose		✓			✓	
	Supplement checklist					✓	

### Outcomes

The main focus of this study, or the primary outcome, is determining the level of MMP-9. The secondary outcomes include examining neuropathy scores and ankle-brachial index (ABI) as well as assessing random blood glucose.

### Randomization and Blinding

After obtaining informed consent and discussing the research objectives, a total of 60 eligible participants will be divided into 2 equal groups. Block randomization with a 1:1 allocation ratio will be used. An assistant will conduct the block randomization, ensuring that both the investigators and participants remain blinded to the intervention allocation. The sequence of the blocks will be generated using a random numbers table. All participants will be randomly assigned to either the intervention group or the placebo group. The manufacturer responsible for preparing the supplements will be requested to label the cans containing either therapeutic cookies or placebos with a unique code.

### Sample Size Calculation

With a significance level (type 1 error) of 5% and a statistical power of 90%, the sample size for each study group will be calculated to be 25, using a 2-sided *t* test, taking into account the changes in MMP-9 values as one of the primary outcomes [20]. We will clarify that the block lengths in our randomization process will be constant. To account for an estimated attrition rate of approximately 20% during the study, the final sample size will be increased to 30 participants in each group. The estimation of the sample size is calculated using the following formula:

In this formula, α=5%, 1-β=90%, SD1=2.7, SD2=2.7, *d*=2.5.

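### Minor arithmetic error: 30 per arm is 25 × 1.2, so 20% attrition leaves 24 completers, one short of the 25 required, and power of about 88% rather than 90%

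*Protocol article*

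**What the plan says.** All the figures are in the protocol article, under Methods.

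- **Error rate and power** (Sample Size Calculation): the two-sided error rate is 5%, and the section plans for "a statistical power of 90" per cent.
- **Evaluable number** (same section): "the sample size for each study group will be calculated to be 25, using a 2-sided" comparison; the method named is the *t* test.
- **Endpoint used for sizing** (same section): the change in MMP-9 from before to after the intervention.
- **Inputs** (same section): "SD1=2.7, SD2=2.7", and a difference *d* of 2.5. The formula itself is not visible in the text at hand.
- **Attrition** (same section): the allowance is for an "estimated attrition rate of approximately 20% during the study, the final sample size will be increased to 30 participants in each group".
- **Total and allocation** (Randomization and Blinding): "a total of 60 eligible participants will be divided into 2 equal groups", by blocked 1:1 allocation. The Intervention section repeats 30 per group.

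**The concern.** An attrition rate is a fraction of those randomised. To finish with a required number, that number must be divided by one minus the rate. Multiplying by one plus the rate always gives too few. The section gives both the evaluable number and the attrition rate, so the two can be checked against the final figure, and they do not agree: the plan's own loss takes each arm below the plan's own requirement.

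What is at stake is the accuracy of the power statement. The section presents 30 per arm as the number that preserves 90% power after about 20% loss, and on its own inputs it does not quite do so.

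**Working it through.** **Inputs.** Two-sided alpha 0.05, power 0.90, SD 2.7 in each arm, difference 2.5, attrition 0.20 and 30 randomised per arm come from Sample Size Calculation. The 1:1 allocation comes from Randomization and Blinding. The difference is 2.5/2.7 = 0.93 SD.

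**Step 1: reproduce the 25.** The normal-approximation formula for two means is

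n = 2 × (z₀.₉₇₅ + z₀.₉₀)² × SD² / d² = 2 × (1.960 + 1.2816)² × 2.7² / 2.5² = 24.51, rounded up to 25.

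This matches the plan. A one-sided 5% test would give 20, and 80% power would give 19, so neither alternative explains the figure.

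**Step 2: reproduce the 30.** 25 × (1 + 0.20) = 30, which matches. The usual correction does not: 25 / (1 − 0.20) = 31.25, so 32 per arm, or 64 in total.

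**Step 3: completers at the stated attrition.** 30 × (1 − 0.20) = 24, one below 25. The attrition that 30 per arm can absorb is:

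- to keep 25: 1 − 25/30 = 16.7%
- to keep 26: 1 − 26/30 = 13.3%

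**Step 4: power.** For the t test, power comes from the noncentral t distribution with 2n − 2 degrees of freedom and noncentrality 2.5 / (2.7 × √(2/n)). At n = 24 the noncentrality is 3.21 with 46 degrees of freedom. The normal-formula power is given for comparison.

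| Completers per arm | Attrition from 30 | t-test power | Normal-formula power |
|---|---|---|---|
| 30 | 0% | 94.1% | 94.8% |
| 26 | 13.3% | 90.6% | 91.6% |
| 25 | 16.7% | 89.4% | 90.6% |
| 24 | 20% | 88.1% | 89.4% |

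At 20% attrition the shortfall from 90% is 1.9 points by the t test and 0.6 points by the normal formula. If each participant drops out independently with probability 0.20, so that completers vary around 24, average t-test power is about 87.8%.

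**Step 5: would baseline adjustment recover the loss?** Statistical Analyses already mentions analysis of covariance. Its gain depends on the correlation ρ between the pre and post values, which the article does not give. Assume that 2.7 is the SD of change and that the pre and post variances are equal. The residual SD is then 2.7 × √((1 + ρ)/2). With 24 per arm:

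| ρ | Residual SD | Power |
|---|---|---|
| 0.5 | 2.34 | about 95% |
| 0.7 | 2.49 | about 93% |
| 0.85 | 2.60 | about 90% |
| 0.9 | 2.63 | just under 90% (89.6%) |
| 0.95 | 2.67 | about 89% |

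The recovery is plausible over much of the range but is not assured.

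**The case against.** The strongest reply is that the slip has almost no practical effect. It costs one completer per arm. Power by the normal formula is 89.4%, and even by the exact t test it stays within 2 points of the target. The attrition is given only as approximate, and 30 per arm does keep 25 completers up to 16.7% loss. Uncertainty in the SD and the difference probably matters more. All of this stands, and it limits the point to a minor correction. It does not remove it, because the section names 20%, and at 20% its own figures disagree.

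A reader might infer several stronger points. The article does not support them.

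- **That 25 is itself wrong because the named t test needs 26.** The t test does reach 90% only at 26. But sizing a t test by the normal approximation is common practice, and the gap is one patient and 0.6 points of power (89.4% against 90%). That the plan used the normal formula is also only inferred from the match, since the formula cannot be seen.
- **That the difference and SD have meaning only as a standardised effect because no unit is printed.** The section cites a source for the MMP-9 sizing that may give the scale, and an article may leave the unit to the full protocol. The two values stand side by side, so a reader can form the ratio of 0.93.
- **That the Mann-Whitney option in Statistical Analyses must lower power further.** That holds under normality. With skewed data the test can be more powerful than the t test, and the plan pairs the choice of test with a normality check.
- **That covariance adjustment guarantees more than 90%.** Step 5 shows that it depends on an unknown correlation.

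**Conclusion.** The point holds as a minor arithmetic error. The inflation multiplies by 1.2 where it should divide by 0.8, so 30 per arm is two short of the 32 needed to keep 25 completers at 20% loss. Power at that loss is about 88% by the two-sided t test, not the stated 90%.

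This rests on the printed inputs (SD 2.7, difference 2.5, two-sided 5%), on equal loss in both arms, and on reading the attrition rate as a fraction of those randomised. It does not show that the trial is materially underpowered: with no attrition, 30 per arm gives 94%, and the target is met up to about 13% attrition.

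**What to change.** Keep 60 participants and correct the statement in Sample Size Calculation. Suggested wording: *30 participants per arm give 94% power with no attrition, at least 90% with up to about 13% attrition (26 per arm), 89% with 16.7% attrition (25 per arm) and 88% with 20% attrition (24 per arm), for a two-sided 5% t test with a difference of 2.5 and an SD of 2.7 (0.93 SD).*

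If the sponsor wishes to cite a gain from analysis of covariance, it should state the assumed pre-post correlation and whether 2.7 is the SD of change, and show power over a range of correlations.

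The cost is one restated sentence. If instead 25 completers are to be secured at 20% loss, the number randomised would have to be 32 per arm, that is 64 in total or four more participants. A shortfall of this size does not require that.

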### Cookies Production

Cookies will be created by following the formula provided by Olawoye et al [21], with some modifications. They will be made with a low glucose ingredient composition, resulting in each cookie containing 51 calories, with a composition of 1% carbohydrates, 6% fat, 4% cholesterol, and 4% fiber, free from gluten, sugar, and salt. Following the optimal conditions for producing gluten-free cookies for patients with diabetes, the cookies are baked at a temperature of 158°C for 20 minutes. The procedure is modified by incorporating 20% Golden Rice extract and 10% *P. crocatum* ethanol extract. Each extract will be prepared using the maceration method with 96% ethanol, and its yield will be calculated. The specific details of the *P. crocatum* extraction procedure are mentioned in a previous study [14].

### Intervention

A total of 60 eligible participants diagnosed with type 2 diabetes will be assigned randomly to either the therapeutic cookies group (n=30) or the placebo group (n=30). Over 14 weeks, participants in the intervention group will take therapeutic cookies (20 g) twice daily, while participants in the control group will take identical placebo cookies. The therapeutic cookies will be provided by Evelyn Food Supplement company, chosen for their reputation for providing high-quality, standardized ingredients, which is essential for the integrity of the study. Both therapeutic and placebo cookies will be indistinguishable in terms of weight, size, shape, taste, color, and odor. The placebo cookies are also produced by Evelyn Food Supplement company. The choice of company was made to maintain the highest research standards and to ensure that there are no conflicts of interest, financial support, or other compensation for the researchers.

The trial will consist of 3 study visits: before the intervention, 1 week after the intervention, and at the end of the intervention period. Study participants will receive instructions on how to use their supplements and will be followed up with phone calls every 3 days throughout the study. Compliance will be assessed by evaluating the number of unused supplements returned by each individual, with the remaining cookies counted to determine total supplement intake. Additionally, participants will be asked to maintain a reporting diary to document any adverse events experienced following the consumption of therapeutic cookies. If any adverse events are attributed to the consumption of therapeutic cookies, participants will be instructed to discontinue taking the supplements and will be promptly referred to a specialist for appropriate treatment. The study participants will not receive any specific dietary recommendations or dietary regimens.

### Blood Sample Collection

Blood samples for the identification of MMP-9 will be collected from each participant at a specific time point in the morning, following an overnight fast. The samples will be drawn at approximately 8 AM to ensure consistency and minimize potential variations in MMP-9 levels due to diurnal rhythms. This fasting state collection will aim to provide a baseline measurement of MMP-9 levels. Additionally, blood samples will be collected both before and after the intervention involving the administration of cookies to assess potential changes in MMP-9 levels in response to the intervention.

### Measures and Measurements

#### Demographic Questions

Participants will be requested to provide information about their gender, age, marital status, the medication and herbs currently being consumed, profession, educational level, distance from the place of residence to the nearest health care service, residence in a city or rural area, duration of having diabetes, and any other diseases or illnesses experienced.

#### Primary Outcome

A blood sample of 5 mL will be collected, and the samples will be centrifuged at 3000 rpm for 5 minutes to separate the serum samples before and after the intervention. The levels of MMP-9 will be determined using western blotting in triplicate. Proteins will be extracted using M-PER Mammalian Protein Extraction Reagent (Thermo; catalog number 87785) according to the manufacturer’s instructions. Protein quantification will be performed using Pierce 660 nm protein assay reagent (Thermo; catalog number 22660). The proteins will be separated on a 10% sodium dodecyl sulfate-polyacrylamide gel electrophoresis and transferred to a polyvinylidene fluoride membrane (Immun-Blot, Bio-Rad). Then, the membrane will be incubated with specific primary antibodies, including anti–MMP-9 (catalog number EP1254; anti-rabbit; 1:500 dilution) and anti–β-actin (catalog number ab8227; anti-rabbit; 1:1000 dilution). Blocking will be performed using 5% skim milk in Tris-Buffered Saline with Tween 20, followed by incubation with the appropriate secondary antibody. The protein bands will be visualized using enhanced chemiluminescence Prime Western Blotting Detection Reagents (GE Health Care; catalog number RPN2232), and the blots will be captured using a Gel Doc machine (Geldoc Syngene Gbox Seri Chemi xrq) [22].

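### The only reference band named for serum MMP-9 is β-actin, a cell protein that does not track serum load; used as the denominator, it would cost precision in the primary endpoint

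*Protocol article*

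**What the plan says.** All from the protocol article.

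- **Outcomes:** "The main focus of this study, or the primary outcome, is determining the level of MMP-9".
- **Primary Outcome, specimen:** blood is centrifuged "to separate the serum samples before and after the intervention".
- **Primary Outcome, preparation:** "Proteins will be extracted using M-PER Mammalian Protein Extraction Reagent", and then "Protein quantification will be performed using Pierce 660 nm protein assay reagent". The section does not say whether the protein measurement sets the load per lane or enters the calculation of the MMP-9 level.
- **Primary Outcome, assay:** "The levels of MMP-9 will be determined using western blotting in triplicate", with chemiluminescent detection. Two primary antibodies are named, one against MMP-9 and "anti–β-actin (catalog number ab8227; anti-rabbit; 1:1000 dilution". The wording leaves the antibody list open, but no other is named.
- **Sample Size Calculation:** 25 per group, "taking into account the changes in MMP-9 values", with an SD of 2.7 in each arm and a difference of 2.5, neither with a unit.
- **Statistical Analyses:** changes in outcome variables are compared between the groups by t test or Mann-Whitney test, and within each group by paired tests.

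**The concern.** β-actin belongs to the cytoskeleton and serves as a loading control for cell or tissue lysates, where its amount follows the amount of cell material in the lane. Serum is cell-free. What β-actin it holds has leaked from damaged cells, in the patient or during the draw and processing. Two lanes loaded with the same amount of serum can therefore show different β-actin bands, and dividing MMP-9 by that band brings the difference into the result. The mammalian extraction reagent in the same section also suggests a lysate workflow carried over to serum.

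This matters because the primary endpoint is a before-after change. Noise in the denominator enters twice, once at each time point, and goes into the SD of the change that drives the power.

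A related point is that chemiluminescent band strength is relative to its own membrane. If a participant's two samples sit on different membranes without a common reference, membrane-to-membrane differences enter the change as well.

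**Working it through.** **1. What is stated and what is inferred**

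| Element | Status in the article |
|---|---|
| Specimen is serum | Stated |
| Western blot in triplicate | Stated |
| Anti-β-actin antibody, with catalogue number and dilution | Stated |
| Another reference band or calibrator | None named |
| Total-protein assay | Stated; its use is not |
| MMP-9 divided by β-actin | Not stated |
| Which samples share a blot; how triplicates are combined | Not stated |

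There are two readings. If β-actin is the denominator, it is unsuited to serum. If it is not, the section names no usable blot reference, and the antibody has no stated purpose. Either way the text needs correcting.

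**2. The plan's own sample size**

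Inputs from Sample Size Calculation: two-sided α = 0.05, power 90%, SD 2.7, difference 2.5.

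n = 2 × SD² × (1.960 + 1.282)² / d² = 2 × 7.29 × 10.507 / 6.25 = 24.51, rounded up to 25 per arm. This agrees with the plan. By the noncentral t distribution, power at 25 per arm is 89.4%.

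**3. Illustration: extra noise in the change score**

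The article gives no assay SD, so the extra noise is an assumption. Let its SD, on the scale of the change, be f × 2.7, and suppose that 2.7 does not already contain it. Then the total SD = 2.7 × √(1 + f²) and the required n = 24.51 × (1 + f²).

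| f (assumed) | Total SD | n per arm for 90% | Power at 25 per arm |
|---|---|---|---|
| 0 | 2.70 | 25 | 89.4% |
| 0.25 | 2.78 | 27 | 87.5% |
| 0.5 | 3.02 | 31 | 81.8% |
| 1.0 | 3.82 | 50 | 62.1% |

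If 2.7 already contains this noise, the first row applies and nothing is lost against the plan. A better reference would then raise power above the stated figure.

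**4. Illustration: blot-to-blot noise**

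With 60 participants, 2 time points and 3 replicates there are 60 × 2 × 3 = 360 lanes. At an assumed 9 to 14 usable lanes per gel, that is 360/14 = 25.7 to 360/9 = 40, or about 26 to 40 blots.

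Let s_b be an assumed between-blot SD per lane, on the same scale as 2.7. If a participant's two samples are on different blots, the variance of the change gains 2 × s_b² when each sample's triplicates share one blot. It gains 2 × s_b²/3 when the triplicates are on three separate blots. If the two samples share a blot, the gain is zero.

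| s_b (assumed) | Power at 25, triplicates on one blot | Power at 25, triplicates on three blots |
|---|---|---|
| 0.5 | 87.3% | 88.7% |
| 1.0 | 81.1% | 86.7% |
| 2.0 | 60.1% | 78.4% |

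These figures show direction and sensitivity only. They concern blot layout, which the article does not describe, and say nothing about the size of the β-actin effect.

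**The case against.** **β-actin may not be the denominator.** The antibody list is open, no division by β-actin is described, and a total-protein assay is planned. This stands, and the point is conditional for that reason. It does not remove the point, because β-actin is still the only reference band named in a section detailed to catalogue numbers and dilutions.

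**Blot layout is a laboratory detail.** A condensed article may leave gel assignment, reference lanes and the handling of replicates to the full protocol or laboratory manual, and the section cites a method source that is not at hand. This also stands. The silence on layout is not an error, and pairing on one blot is offered only as an improvement. A reader might infer that each participant's two samples will run on different blots, or that all baseline samples form one batch and all follow-up samples another. Nothing in the article says so.

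**The trial may not be underpowered for this reason.** A reader might take the tables above as a measured loss. They are not: every loss rests on an assumed SD, triplicates may absorb part of the noise, and 2.7 may already include it.

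**The randomised comparison is not biased.** A reader might infer that a poor reference band makes a false treatment effect. Noise unrelated to arm widens the confidence interval but does not shift the difference between arms. Drift between a baseline batch and a follow-up batch, if it occurred, would affect both arms alike. It would distort only the within-group tests.

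**Conclusion.** The point holds in limited form. For a serum endpoint, the article names a reference band that does not measure serum load. If that band is the denominator, the change in MMP-9 carries avoidable variation.

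The harm is lost precision of unknown size, anywhere from none relative to the plan (if 2.7 already contains the noise) upwards. Lack of bias between arms rests on the β-actin signal and the placement on blots being unrelated to allocation; nothing in the article suggests otherwise. The stated 25 per group reproduces from its inputs and is not in question here. The change should be made because it is cheap and protects the primary endpoint, not because a given power loss has been shown.

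**What to change.** 1. Replace β-actin with total-protein normalisation: load equal total protein per lane by the 660 nm assay already planned, and normalise each MMP-9 band to a total-protein stain of the membrane.
2. State in the Primary Outcome section how band intensity becomes the MMP-9 level, with the mean of the triplicates as the single value per participant and time point.
3. As a low-cost addition, run each participant's before and after samples on the same blot, with both arms represented on every blot and one pooled-serum reference lane.

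Cost: one lane per gel, a stain and a planned gel layout. No extra blood, visits or participants are needed. If power figures for assay noise are reported, label them as illustrations under assumed SDs.

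### The western-blot description for MMP-9 places blocking after the primary antibodies; followed as written, every primary-outcome reading is exposed to avoidable non-specific background

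*Protocol article*

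**What the plan says.** The Outcomes section makes MMP-9 the primary endpoint: "The main focus of this study, or the primary outcome, is determining the level of MMP-9". The Primary Outcome section names the assay: "The levels of MMP-9 will be determined using western blotting in triplicate". Under Blood Sample Collection, "blood samples will be collected both before and after the intervention involving the administration of cookies", so the assay supplies both the baseline and the follow-up reading.

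The Primary Outcome section then describes the blot step by step. After gel separation the proteins are "transferred to a polyvinylidene fluoride membrane (Immun-Blot, Bio-Rad"). The next sentence reads "Then, the membrane will be incubated with specific primary antibodies, including anti–MMP-9", together with an antibody to β-actin. The sentence after that is "Blocking will be performed using 5% skim milk in Tris-Buffered Saline with Tween 20, followed by incubation with the appropriate secondary antibody". Chemiluminescent detection and image capture follow, and the paragraph closes with a literature citation.

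The Sample Size Calculation section sizes the trial on changes in MMP-9: "In this formula, α=5%, 1-β=90%, SD1=2.7, SD2=2.7, *d*=2.5", with 25 per group before allowance for attrition.

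**The concern.** Blocking coats the free protein-binding sites on the membrane so that antibody added later binds its target and not the membrane itself. It has to come before the primary antibody to do this. In the written order the primary antibodies are applied to a bare membrane. Whatever binds there non-specifically is then made visible by the secondary antibody, and blocking afterwards does not remove antibody already bound.

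This is the assay for the one endpoint that determines the sample size. If the background differs between membranes, lanes or runs, it enters the measured change in MMP-9 as extra variance and makes a true difference harder to detect.

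**Working it through.** **Step order.** The article gives no figure for this point, so the check is a reading of the text.

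| Step | Where it stands in the Primary Outcome section | What fixes its place |
|---|---|---|
| Transfer to the membrane | End of the gel-separation sentence | No blocking mentioned here |
| Primary antibodies (anti-MMP-9 1:500, anti-β-actin 1:1000) | Next sentence, "Then, the membrane will be incubated with specific primary antibodies" | Its opening adverb ties it directly to transfer |
| Blocking, 5% skim milk | Sentence after that | Sentence order |
| Secondary antibody | Same sentence as blocking | Stated to follow blocking |
| Detection and image capture | Last sentence | Sentence order |

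No other section mentions blocking, and no antibody diluent is named that might contain a blocking agent. The only blocking step in the article therefore stands between the primary and the secondary antibody.

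**Planning figure, for context.** Inputs from the Sample Size Calculation section: two-sided α = 5%, power 90%, SD = 2.7 in both groups, d = 2.5.

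- n per group = 2 × SD² × (z₀.₉₇₅ + z₀.₉₀)² / d² = 2 × 7.29 × (1.960 + 1.282)² / 6.25 = 24.5, rounded up to 25. The stated 25 is reproduced.
- Power at 25 per group: 90.6% by the normal approximation, 89.4% by the noncentral t distribution with 48 degrees of freedom.

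**Illustration under an assumption.** The article gives no assay error and no data on background. Suppose that uneven background adds a fraction f of the planning variance, so that SD = 2.7 × √(1 + f). The values of f are not from the document.

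| Assumed f | Variance | SD | d/SD | Power, n = 25 per group (noncentral t) |
|---|---|---|---|---|
| 0 | 7.29 | 2.70 | 0.926 | 89.4% |
| 10% | 8.02 | 2.83 | 0.883 | 86.4% |
| 20% | 8.75 | 2.96 | 0.845 | 83.4% |
| 30% | 9.48 | 3.08 | 0.812 | 80.3% |

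The result depends heavily on the assumption. If the SD itself, and not the variance, rose by 10%, 20% or 30%, the normal-approximation power would fall from 90.6% to 84.5%, 77.9% or 71.2%. The article gives no basis for preferring either set.

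**Constant background.** If the same amount b is added to a participant's reading before and after, the change is (post + b) − (pre + b) = post − pre. A constant additive background cancels in a simple difference. Only background that varies between the readings being compared adds noise.

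**The case against.** The strongest reply is that this is a sentence-order slip and not a laboratory choice. The blocking sentence has no time marker of its own linking it to the sentence before, so its place after the primary antibodies rests on the order of the sentences. The paragraph is also a condensed account: it gives no washes, incubation times or temperatures, and it ends with a citation whose content is not available. No laboratory could run the assay from this text alone, and the working procedure may well be correct.

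Much of that stands. Nothing shows that anyone chose to leave the membrane unblocked. It does not remove the point, because the article does not leave blocking to another document: it states the step, with reagent and concentration, in a place where it cannot serve its purpose.

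A reader might go further and infer three things that the document does not support.

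- *That MMP-9 readings will be distorted.* The text shows exposure to background, not the presence of any.
- *That background will shrink the measured treatment effect.* That would apply to a relative fall. The Sample Size Calculation and Statistical Analyses sections refer to changes in the outcome, with no percentage measure named, and constant background cancels in a difference. If readings were expressed relative to β-actin, background would enter numerator and denominator, and the net direction could not be predicted from what is given.
- *That the comparison between arms is biased.* One procedure covers both arms and both time points, so the expected consequence is noise common to both.

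Triplicate measurement would average out part of any replicate-level noise. It would not remove background shared by the three replicates.

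**Conclusion.** The point holds as a misplaced step in the stated method for the primary outcome. Followed literally, the text puts the primary antibodies on an unblocked membrane and so exposes every MMP-9 reading to avoidable non-specific background. Uneven background would add non-differential noise to the primary comparison.

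The size of the effect cannot be derived from the document. The fall in power from 89% to between 86% and 80% rests wholly on the assumed 10% to 30% increase in variance, and on SD and d values whose relation to blot intensity the article does not explain. It illustrates the direction and is not an estimate. The absence of bias between arms rests on the same procedure being used for all samples and on the blots being processed and read without knowledge of allocation. No change to the sample size follows from this point.

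**What to change.** In the Primary Outcome section, rewrite the sequence as transfer, blocking with 5% skim milk, primary antibodies, wash, secondary antibody, detection. If the laboratory does something else that serves the same purpose, such as including a blocking agent in the antibody diluent, state that procedure instead. Say that this one procedure applies to all samples from before and after the intervention in both groups. If any samples have already been blotted, confirm which order was used.

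The cost is an edit to the text: no new reagents, samples or participants, and no change to the analysis.
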